## Materials and methods

### Study design

A multicentre prospective study with a 12-month follow-up period will be conducted in the three Dutch burn centres: Maasstad Hospital Rotterdam, Red Cross Hospital Beverwijk, and Martini Hospital Groningen. Patients with deep partial-thickness burns, scanned as yellow by Laser Doppler Imaging (LDI), will be monitored during 18 months; two nine-month periods with either therapy as the treatment of choice in one of the periods. This time period was chosen based on expected numbers and project logistics, such as staffing. Standard care in the Netherlands for deep partial-thickness burns is predominantly conservative treatment with delayed excision and grafting if needed. However, early excision and grafting is applied if deemed more appropriate for a specific patient. The first nine-month period (July 15^th^ 2022 to April 14^th^ 2023) this strategy is followed. In the following nine-month period (April 15^th^ 2023 to January 14^th^ 2024) clinical practice will be changed: early excision and grafting will be the primary treatment. However, in specific cases e.g. based on clinical expertise, conservative treatment can be applied. Depending on the received treatment, patients will be categorized as either the conservative treatment group with delayed excision and grafting if needed, or the early excision and grafting group.

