### Participants

#### Selection

Neither, randomisation nor blinding will take place. The used treatment strategy determines to which group the patient is assigned. The first group represents conservative treatment with delayed excision and grafting if needed, the second group represents early excision and grafting. If a patient is eligible for the study, a member of the research team will provide information about the study. The patient is asked for consent to take additional measurements 12 months after discharge. After reflection time and written informed consent, the patient is included.

Anyone using the protocol must consider the ethical implications of the timing of surgery in their own practice setting. To ensure patient safety, the attending physician is justified in deciding not to start or discontinue treatment from the allocated treatment, based on sound medical grounds and after consulting with the health care team. Deviation from the assigned treatment should be rare, and the reason must be thoroughly documented.

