#### Burn wound area selection

Based on the healing potential, the attending physician will determine whether the patient has burns that meet the inclusion criteria. A maximum of two inclusion criteria-meeting burns per patient are followed for the study.

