#### Surgical technique

Excision and grafting are carried out in accordance with the local protocol of the operating burn centre. Burns will be tangentially excised using guarded knives and/or hydrosurgery. Autografts are harvested with an electrical dermatome from a preoperatively selected donor site. Autografts will be predominantly meshed. Postoperative care is equal for both treatment groups.

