### Statistical analysis

For the statistical analysis descriptive statistics will be used. All parameters will be tested for normality. Depending on the distribution of the data, a mean and standard deviation (normal) or a median and interquartile range (skewed) will be displayed. Differences between the two treatment strategies for the primary outcome measure scar quality and other outcomes will be analysed using two-sided T-test (normally distributed continuous data) or Mann-Whitney U-test (skewed continuous data), and two-sided Chi-square test or Fisher’s exact test (categorical data). Differences between groups in time to event outcomes (i.e. time to surgical intervention and time to wound healing) will be analysed using Kaplan-Meier regression. To correct for the possible influence of patient, burn, and burn centre characteristics on the results, multivariate linear regression (continuous data), multilevel logistic regression (categorical data), and Cox regression (time to event data) will be used. If possible, exploratory analyses will be done on the 10–14 day surgery group. Data analysis will be performed using IBM Statistical Package for the Social Sciences (SPSS) version 26 (SPSS, Chicago, IL, USA) and Python (Python Software Foundation, Delaware, USA).

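### If burn centre is the level in the multilevel logistic model, three centres are too few for a random intercept to remove centre confounding; enter centre as a fixed factor

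*Protocol article*

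**What the plan says.** All of this is in the protocol article.

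- **Aim of the adjusted models** (Statistical analysis): "To correct for the possible influence of patient, burn, and burn centre characteristics on the results".
- **Models named** (same sentence): linear regression for continuous data, then "multilevel logistic regression (categorical data), and Cox regression (time to event data) will be used". Only the logistic model is called multilevel. The level is not named, nor is it said whether centre enters as a random or a fixed term.
- **Centres** (Study design): the study "will be conducted in the three Dutch burn centres".
- **Groups** (Study design): "Depending on the received treatment, patients will be categorized as either the conservative treatment group" or the early surgery group. Under Selection: "Neither, randomisation nor blinding will take place".
- **Local practice** (Surgical technique): "Excision and grafting are carried out in accordance with the local protocol of the operating burn centre". The section on conservative treatment likewise leaves topical agents and dressings to local protocol.
- **Other possible clustering**: "A maximum of two inclusion criteria-meeting burns per patient are followed for the study" (Burn wound area selection), and questionnaires repeated over time (Patient reported outcomes).

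**The concern.** Most categorical outcomes under Clinical outcomes occur once per patient: death during admission, readmission, reoperation, transfusion, sepsis, shock. A patient-level random effect has nothing to cluster in such data, so the only grouping the article offers for a multilevel model is centre.

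A random intercept over three centres needs a variance estimated from three units. Maximum likelihood often puts it at zero, and the model then makes no centre adjustment. When the estimate is positive, centre effects are pulled towards their mean, so the adjustment is incomplete.

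This matters here because nothing balances centre between the groups by design. Local protocols give a route from centre to outcome. Grouping by treatment received, with clinicians free to depart from the period's strategy, gives a possible route from centre to treatment. If both are active, the adjusted odds ratio reports part of the centre difference as an effect of early surgery. The Discussion says the results will feed a decision aid and a cost-effectiveness study.

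**Working it through.** The plan has no figure of its own to reproduce on this point. Its only relevant number is the expected maximum of 204 patients, which is not disputed.

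**Inputs from the article:** 3 centres; at most 204 patients; groups by treatment received; no randomisation.

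**Assumptions, none given in the article:** equal centres of 204/3 = 68; true treatment log odds ratio 0; event rate in the middle centre 30% or 10%; share treated early by centre 30/50/70% or 20/50/80%; centre effects −d, 0, +d on the logit scale with d = 0.25, 0.5 or 1.0.

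**Model:** logit P(event) = a + b·(early surgery) + c_j for centre j. Three maximum-likelihood fits were compared: no c_j; c_j ~ N(0, σ²); and c_j as two indicators.

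**One case by hand** (30%, uptake 30/50/70%, d = 0.5):
- Centre logits are −0.847 − 0.5, −0.847 and −0.847 + 0.5, so event probabilities are 0.206, 0.300 and 0.414.
- Early patients: 20.4, 34 and 47.6. Expected events: 4.21 + 10.20 + 19.71 = 34.12 of 102.
- Conservative patients: 47.6, 34 and 20.4. Expected events: 9.82 + 10.20 + 8.45 = 28.47 of 102.
- Unadjusted log odds ratio: ln(34.12/67.88) − ln(28.47/73.53) = −0.688 + 0.949 = 0.261, all of it confounding.
- On the same expected counts the random intercept gives 0.134 (0.134/0.261 = 51% left). Centre indicators give 0.000.

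**If uptake is equal across centres**, for example 50% in each, both arms have 34 patients per centre and 34 × (0.206 + 0.300 + 0.414) = 31.3 expected events. The unadjusted log odds ratio is then 0 and there is nothing to remove.

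**Simulation**, 300 data sets per scenario. Entries are mean log odds ratios; share left = random intercept / unadjusted.

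| Event rate | Uptake % | d | Unadjusted | Random intercept | Centre fixed | Share left | Variance ≈ 0 | SD random / fixed |
|---|---|---|---|---|---|---|---|---|
| 30% | 30/50/70 | 0.25 | 0.137 | 0.101 | 0.007 | 73% | 62% | 0.32 / 0.33 |
| 30% | 30/50/70 | 0.5 | 0.266 | 0.118 | 0.007 | 44% | 21% | 0.34 / 0.34 |
| 30% | 30/50/70 | 1.0 | 0.506 | 0.056 | −0.015 | 11% | 0% | 0.35 / 0.36 |
| 30% | 20/50/80 | 0.25 | 0.218 | 0.168 | 0.016 | 77% | 66% | 0.33 / 0.35 |
| 30% | 20/50/80 | 0.5 | 0.376 | 0.184 | −0.023 | 49% | 27% | 0.39 / 0.38 |
| 30% | 20/50/80 | 1.0 | 0.742 | 0.106 | −0.016 | 14% | 0% | 0.38 / 0.38 |
| 10% | 30/50/70 | 0.25 | 0.152 | 0.130 | 0.038 | 85% | 73% | 0.50 / 0.52 |
| 10% | 30/50/70 | 0.5 | 0.211 | 0.106 | −0.055 | 50% | 45% | 0.51 / 0.52 |
| 10% | 30/50/70 | 1.0 | 0.524 | 0.184 | 0.046 | 35% | 6% | 0.53 / 0.51 |
| 10% | 20/50/80 | 0.25 | 0.255 | 0.207 | 0.062 | 81% | 74% | 0.50 / 0.56 |

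The Monte Carlo standard error of the random-intercept mean is 0.018 to 0.030. Two planned scenarios (10%, 20/50/80%, d = 0.5 and 1.0) were not completed. On expected counts the fixed-effect bias was 0.000 in all ten.

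A separate simulation (400 data sets per setting, event rate 15–30%, uptake 30/50/70%, centre log-odds −0.4/0/+0.4) agrees in direction: 0.22–0.24 unadjusted, 0.13–0.14 with the random intercept, about 0 with centre indicators, and variance near zero in 32–50% of data sets. Its more extreme setting (20/50/80%, ±0.5) left 0.21–0.27, with a type I error of about 10% against 3–5%. The upper end therefore depends on the settings chosen.

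**The case against.** The strongest reply is that the article never says centre is the random level. Patient is another candidate: up to two burns are followed per person, wound infection is recorded per study area, and questionnaires are repeated. Centre could also sit in the same model as a fixed covariate, in which case the bias argument falls away. This stands as a limit. It does not dispose of the point, because for outcomes recorded once per patient a patient level is empty and centre is the only level left.

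The second reply is that unequal uptake is not shown. Study design gives one change of strategy on common dates for all centres, and Selection says deviations should be rare. That also stands: the uptake figures above are assumptions, and clinical discretion makes unequal uptake possible, no more.

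Third, the share left is largest where the centre effect, and so the confounding to be removed, is small. At a 30% event rate with d = 1.0 only 11–14% remains. A bias of 0.118 against an SD of 0.34 is about a third of the estimate's own spread (0.118/0.34 = 0.35).

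A reader might also infer that the linear and Cox models ignore centre, or that the primary outcome is affected. The article supports neither. Its stated aim of correcting for centre covers all three model types, and the scar score, if analysed as continuous, goes to linear regression.

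**Conclusion.** The point holds conditionally. If centre is the random level, and if uptake of early surgery differs by centre, the random intercept removes only part of the centre confounding. About half is left at moderate centre effects (44–50% at d = 0.5), with a range of 11–85% over the ten completed scenarios. The bias left is about 0.06 to 0.21 in the log odds ratio, that is, odds ratios of about e^0.06 = 1.06 to e^0.21 = 1.23 where the truth is 1. The centre variance collapses to about zero in 62–74% of data sets at d = 0.25, 21–45% at d = 0.5 and 0–6% at d = 1.0. With equal uptake there is no centre confounding.

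It would be too strong to say that this study's adjusted odds ratios will be biased; the documents show neither the level nor the uptake by centre. The better method is nonetheless clear, because centre indicators remove the problem in every scenario with nearly the same precision. The point is confined to adjusted categorical secondary outcomes and leaves confounding by indication and by period untouched.

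**What to change.** In the Statistical analysis section:

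- Replace the multilevel logistic model by logistic regression with burn centre as a fixed factor (two indicators).
- Use the same two indicators in the linear models, and enter centre as a factor or stratum in the Cox models, so that centre is handled alike for all outcome types.
- Keep a random effect only for patient, where two study areas or repeated questionnaires per patient are analysed, and name that level.

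The cost is a change to one sentence and two degrees of freedom per model. The SD of the estimate barely changes: 0.34 against 0.34 in a typical case, and 0.56 against 0.50 in the least favourable. For rare outcomes such as death or sepsis, centre indicators can produce cells without events, so a penalised fit (for example Firth) should be named for that case.

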### Ethical considerations and declarations

In consultation with the medical ethics committee, it was agreed that the treatment strategies are part of usual care. Therefore, a medical ethics request was made solely for the conduction of the POSAS 12 months after discharge. The Medical research Ethics Committees United (MEC-U) has confirmed that the Medical Research Involving Human Subjects Act (WMO) does not apply to this study (W23.039) on March 14^th^ 2023. The study protocol was approved by the local review boards of all participating hospitals: Maasstad Hospital Rotterdam (L2023027), Red Cross Hospital Beverwijk (23.010), and Martini Hospital Groningen (2023–080).

### Study status and timeline

Data collection from DBR R3 and BORN started on July 15^th^ 2022. Inclusion of participants started after approval of the local review boards of all participating hospitals on June 25^th^ 2023. The first patient inclusion and 12-month POSAS was conducted on June 30^th^ 2023. Data collection and participant selection is expected to be completed in January 2025.

## Discussion

In this protocol we described the aim and specific design attributes of our study to address the gaps in understanding regarding the timing of surgical intervention after deep partial-thickness burn injury. In particular, we intend to compare long-term scar quality, clinical outcomes, and patient-reported outcomes evident after conservative treatment with delayed excision and grafting if needed, and early excision and grafting of deep partial-thickness burns in Dutch burn care. While patient-reported outcomes on this topic are scarce, this study focuses on long-term patient-reported outcomes that will be measured using the POSAS 3.0 and the BORN [38]. POSAS is a unique scar quality assessment tool, as it not only includes the professional’s perspective but also incorporates the patient’s view [39]. BORN provides a wide range of outcomes that were considered important by patients, healthcare professionals, and researchers (Spronk et al, submitted). This will provide insight into the outcomes related to timing of surgical intervention to enable healthcare providers to offer patients more in-depth information when surgery is discussed. The study findings are aimed to support shared decision making in person-centred burn care.

A strength of this study is the multicentre design which improves generalizability and applicability to similarly resourced burn care facilities. Additionally, the homogeneity of the included study burn wound areas is another strength of the study. The followed burns are all deep partial-thickness burns with a comparable healing potential.

A possible limitation might be the absence of donor site quality as an outcome. However, it was deliberately chosen not to include this, since ample literature regarding this topic is available and a recent study on long-term patient-reported scar quality of donor sites was conducted in one of the participating burn centres [13].

Regarding considerations for collaborative research: by publishing this study protocol, we aim to encourage authors from other countries to conduct similar studies. Multisite studies can enhance the generalisability of findings and improve evidence-based burn care [40]. This study protocol leaves room for translation to a randomized controlled trial (RCT). However, we decided not to conduct an RCT due to the niche sector of burn care and to increase the external validity of our results by collecting real-world data. Therefore, we encourage other authors to use real-world data for answering the optimal surgical timing research question. The POSAS was chosen for the direct assessment of scar quality because of its reliability, validity, and feasibility. It is recommended to use the POSAS for long-term scar quality assessment, provided that personnel are trained in conducting it. One could choose for standardized images with a ruler as outcome measure, but this was not selected in this study due to their difficult comparability and the availability of trained POSAS personnel.

The findings of the described study add to the ongoing worldwide debate on the optimal treatment strategy for deep partial-thickness burns. Furthermore, the results of this study will be included in a cost-effectiveness study and in the development of a decision aid for shared decision making on timing of surgery in acute burns. The decision aid will support the patient and healthcare provider in the decision for the optimal treatment based on the patients’ goals and preferences.
